### Massage therapists

All massage treatments will be performed by licensed massage therapists who have at least 5 years experience, are comfortable strictly following both treatment protocols, and are trained and experienced in the techniques permitted in both the RM and FSM treatment protocols. Approximately 25 massage therapists in the Puget Sound region of western Washington will be recruited from within the network of alternative providers contracted to provide services to Group Health members. This will ensure that the therapists have already met minimum qualifications (e.g., massage training and licensure, malpractice insurance coverage, accessible and adequate treatment facilities). Participating massage therapists will need to agree to strictly adhere to the treatment protocols, be comfortable providing either massage treatment to any of the study participants, and to complete the training program for the study.

### Training and monitoring of massage therapists

The massage therapists will attend 1.5 day training program with co-investigators [name] and [name], and consultant [name], an experienced massage therapist who is a national leader in developing standards of care for the profession. This training will include a thorough discussion of the protocol and instruction in using terms consistently when they record the findings of their assessments and the treatments they provide on the treatment visit forms. There will also be hands-on training sessions to ensure that study massage therapists are comfortable with following both of the protocols and with the types of questions they might be asked by participants about the protocols. The therapists will also practice completing the treatment forms correctly and giving self-care suggestions. The training sessions will include "dress rehearsals" for both of the treatment styles using mock participants.

### Assessment of outcomes

A core set of recommended outcome measures [9] covering five important domains will be assessed: back-related dysfunction, pain, general health status, disability and patient satisfaction. The primary effectiveness outcomes are pain and dysfunction assessed at the 10-week telephone interview. Relative effectiveness will be determined by comparing changes from baseline to follow-up among the three treatments arms. Table 3 summarizes the categories of questions included in the baseline and follow-up questionnaires.

**Table 3 T3:** Content of baseline and follow-up questionnaires

**Measures**	**Baseline**	**10-Week**	**26-Week**	**52-Week**
Sociodemographic characteristics	x			

Body mass index (height, weight)	x			

Current smoking status	x			

Back pain history	x			

* Roland Disability Questionnaire (dysfunction)	x	x	x	x

* Bothersomeness of low back pain	x	x	x	x

Satisfaction with back care	x	x	x	x

General Health Status (SF-12)	x	x		x

Disability days	x	x	x	x

Medication use	x	x	x	x

Worry about back problem	x	x	x	x

Exercise (Back-related, general)	x	x	x	x

Confidence in ability to self-manage future back pain	x	x		x

Perceived Stress (PSS)	x	x	x	x

Fear Avoidance (Tampa Scale)	x	x	x	x

Psychological Distress (MHI-5)	x	x	x	x

Global Rating of Improvement		x	x	x

Expectations of treatment	x			

Knowledge of massage	x			

Adverse experiences		x		

Perceptions of massage experience (massage arms only)		x	x	x

Use of non-health plan services for back pain		x	x	x

Use and cost of health plan services for back pain [from automated databases]				

* Co-primary outcome measures

### Primary measures of effectiveness

The modified Roland-Morris Disability Questionnaire will be used to measure back-related patient dysfunction [9,10]. This instrument, which asks 23 yes/no questions and takes approximately five minutes to complete, is scored by summing up the number of "yes" responses. It has been found to be reliable, valid and sensitive to clinical changes [10-12] and is well suited for telephone administration. This is the single most important outcome of the study.

Because there are individuals who are very bothered by even a small amount of pain and others who are not bothered by even moderate pain, our primary measure of symptoms assesses participants' perceptions of the impact of pain on their lives rather merely assigning a pain severity score. Thus, participants will be asked to rate how bothersome their low back pain has been during the past week on a 0 to 10 scale where 0 represents "not at all bothersome" and 10 "extremely bothersome". This measure appears to have substantial construct validity - i.e., it is highly correlated with measures of function and other outcome measures [10].

Both primary outcomes will be measured at baseline and during the 10, 26 and 52 week follow-up interviews. The trial's primary endpoint will be the 10 week follow-up, immediately after completion of the 10 massage treatments. All interviews will be conducted using computer-assisted telephone interviews (CATI)

### Secondary outcome measures

*General health status *will be measured using the well-validated SF- 12 [13] that has been recommended for use in studies of back pain [14]. We will calculate the SF-12 physical and mental health summary scores.

*Days of restricted activity due to back problems*, a surrogate for disability, will be measured with a back-pain specific modification of 3 National Health Interview Survey questions about the number of half-days spent in bed, home from work or school, or cutting down on usual activities due to illness or injury during the past week [15].

Patient global rating of improvement will be measured by asking participants to provide a global rating of improvement in their back-related dysfunction on a seven point scale ranging from "completely gone" to "much worse". Satisfaction with information given about the cause of the back problem, treatments received, and overall care will be measured using three separate questions, each using a 5-point Likert scale (ranging from very satisfied to very dissatisfied).

We will include the following psychosocial measures:

*Psychological distress *will be measured with the 5-item Mental Health Index of the SF-36 [16]. This scale, which assesses general mental health, including depression, anxiety, behavioral-emotional control, and general positive affect, is brief and reliable and has shown good agreement with more comprehensive measures of mental health [17].

*Perceived stress *will be measured with the 10-item version of the Perceived Stress Scale [18], the most widely used self-report measure of psychological stress. The Perceived Stress Scale is a state measure that usually asks about stress experienced over the last month, and is influenced by factors that vary such as daily hassles, life events, appraisals and coping resources [19]. Thus, the PSS should be sensitive to changes in life stress due to the massage intervention.

*Fear avoidance *will be measured with the Tampa Scale for Kinesiophobia [20] that measures back pain patients' fears of movement, exercise and serious underlying disease. We will use the 10-item version that retains acceptable internal consistency (alpha = 0.76), is easier and quicker to administer and has proved sensitive in detecting intervention effects in clinical trials [21]. Typical items (rated on a "strongly agree" to "strongly disagree" Likert scale) are: "I'm afraid that I might injure myself if I exercise;" and "My body is telling me I have something dangerously wrong."

### Measures of health care resource use

Participants' use of health care for back pain during the year following randomization will be measured using automated utilization data, interview data on out-of-plan utilization, and records for each visit to the study massage therapists. The automated utilization data will provide information about all provider visits and hospitalizations at health plan facilities or paid for by the health plan. Visits for back pain can be identified by the diagnoses listed for every visit and hospitalization. Imaging studies of the lower back can also be identified by specific procedure codes.

Visits to non-study massage therapists and providers not covered by the health plan will be estimated from the interview data for the time period since the previous interview, i.e., the 10-week interview will request information about out-of-plan utilization since participants were randomized to study treatment, the 26-week interview will ask about the previous 16 weeks, etc. These data will permit determination of the percentage of participants in each treatment group who had any visits for low back pain during and following the intervention period, as well as calculation of the mean number of visits. Current use of medications of all types used for low back pain will be captured in the follow-up interviews.

Costs of back-related care will be estimated by assigning dollar values to each service. Costs of specific services (e.g., visits, imaging studies, medications) will be determined using data from Group Health's cost management information system which defines cost based on standard relative value units (RVUs) assigned to actual department RVUs produced. Costs of the massage interventions will be distinguished from the costs of all other back pain-related services to permit separate comparisons among the treatment groups of the costs of the interventions themselves, of the non-intervention back care costs incurred during the 10-week treatment period, and of the total back pain-related costs incurred over the 42 week period between completion of the study interventions and the end of the 52 week follow-up period.

### Data Collection and Management

We will collect information on the outcomes at every stage of our recruitment, randomization, and treatment process so we can report patient flow according to the CONSORT guidelines [22]. Specifically, we will record the number of invitation brochures sent, the number of responses received, the resolution of these responses (ineligible, refused, eligible and randomized, other), the number of participants assigned to a massage treatment who were actually treated, the number of visits made, the number of participants providing follow-up data by group at each follow-up, the number of participants completing the trial, and the number of withdrawals due to: ineffective treatment, adverse experiences, loss to follow-up, or other causes.

We will implement procedures to ensure that randomization is proceeding as planned, recruitment is on track, clinic data collection forms are accurately entered into databases, the computer assisted telephone interviewing (CATI) system is storing data correctly, and data can be accurately transferred and retrieved as needed. We will develop a relational database to track information on every stage of recruitment, randomization, treatment process, and outcomes assessment so we can report patient flow automatically and in an integrated fashion using standard, automated reports. To ensure accurate transfer of information, we will use electronic methods to routinely transfer data from the CATI database to the relational database. All data system processes will be thoroughly tested prior to the start of recruitment.

The CATI programs will contain range and logic checks. Appropriate information collected on the massage treatment visit forms will be entered into a computer database that also contains range and logic checks. Data will be examined for completeness using computer programs developed specifically for that purpose. In addition, we will test all analytic programs to ensure that the analyses are accurate. Procedures to protect the confidentiality and integrity of the databases and paper systems will be reviewed by the biostatistician prior to patient recruitment and periodically during the study.

To maintain the confidentiality of patient-related information in the database, unique participant study numbers will be used to identify patient outcomes and treatment data. The password security system will assign appropriate levels of computer privileges to different groups of database users. This will ensure that all masked personnel remain masked to treatment group.

Computer files with patient names will be password protected with access restricted to staff using this information to recruit patients, obtain follow-up data, and interact with any patients reporting adverse events. We will pre-test the procedure for sending the randomization information to the massage therapist and regularly audit treatment visit forms to ensure that participants being treated by massage therapists receive the treatment to which they were assigned and that the protocol is being correctly followed. During the treatment phase of the trial, we will continually monitor the massage therapists and provide focused booster training as needed. The massage therapists will mail copies of Visit Forms (identified only by study ID number and patient initials) to the research team after each participant has completed treatment. After being audited to ensure adherence to the protocol, charts will have initials removed, and again stored in locked filing cabinets accessible only to study personnel. Finally, all analysis data files will be password protected. Full data backup procedures will be performed nightly.

### Protection of human subjects and assessment of safety

#### Protection of human subjects

This study protocol was approved by the Institutional Review Board of Group Health Cooperative.

#### Data Safety Monitoring Body

Given the favorable safety profile from previous studies of massage coupled with the small numbers of adverse events reported in the literature, this trial will be monitored for safety by an independent Data Safety Monitoring Body (DSMB) comprised of a biostatistician, primary care physician and massage therapist. The DSMB's job will be to evaluate the adverse experience data we will provide them on a regular basis to protect the safety of the study participants. Based on the observed adverse effects of the treatments under study, the DSMB will make recommendations on a regular basis to the P.I. and the Office of Clinical and Regulatory Affairs at the National Center for Complementary and Alternative Medicine (NCCAM) regarding continuation, termination, or other modifications of the trial.

#### Adverse Events

Participants will be asked about adverse experiences at each massage visit and during the 10-week telephone interviews. We will define an adverse experience as any unfavorable and unintended sign, symptom or disease temporally associated with the use of the massage treatments that could reasonably be related to the treatments. Because massage has relatively short-term physiological effects, we will not report adverse events that first manifest more than one week after a participant's final treatment (or more than 10 weeks after randomization for the usual care control group). If a participant develops a Serious Adverse Experience (i.e., any adverse event occurring during treatment that results in any of the following outcomes: death, a life-threatening adverse event, inpatient hospitalization or prolongation of existing hospitalization, a persistent or significant disability/incapacity, or cancer) during the 10 weeks after randomization, it will be promptly (within 7 days) reported to the chair of the Data Safety Monitoring Body. If the Adverse Experience is, at least possibly, due to massage, it will also be promptly reported to the Group Health IRB and to NCCAM's Office of Clinical and Regulatory Affairs. In addition, we will summarize all adverse experiences in the trial in our routine reports to our DSMB and IRB.

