### Randomization to treatment groups

After administering the baseline questionnaire, the RS will use an ACCESS database to randomize one third of the participants to usual care and two-thirds to a massage intervention. The RS will ask the participants randomized to a massage treatment about their preference for geographic location of a therapist. The RS will then identify a therapist in the chosen location and enter that therapist's study identification code into the ACCESS database program that will use a pre-programmed computer-generated sequence of blocked random numbers for each therapist to assign the participant, with equal probability, to FSM or RM treatment. Thus, using this two-stage randomization procedure, roughly one-third of all participants will be randomized to each of the three arms. This will also ensure that each massage therapist sees approximately equal numbers of participants in each of the two massage groups. The one-third of participants randomized to the control group will be mailed checks for $50. The randomization database will be built to ensure that treatment allocation cannot be viewed prior to randomization and cannot be changed after randomization.

Participants randomized to the control group will be thanked for their willingness to participate, reminded of the importance of completing the follow-up interviews, and told they will be mailed checks for $50 in 4 to 6 weeks. Shortly after randomization to massage, the RS will call the massage therapist to provide the participant's contact information and to specify which type of massage the participant is to receive. The RS will also give the massage therapist a date by which the first appointment needs to be scheduled for that participant. Participants randomized to a massage treatment will be telephoned within 48 hours by the chosen massage therapist to set up the initial appointment. The massage therapist will call the research assistant to confirm that the first appointment has been made. The massage therapist will provide participants directions to the therapist's office. The massage therapist will schedule the nine subsequent visits with the participant.

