### Study Treatments

Participants will be randomized to one of three groups: RM, FSM or UC. The RM and FSM treatment protocols will maximize the distinction between the types of relaxation massage and focused structural massage employed by licensed practitioners but preserve the massage therapists' belief that they are providing potentially helpful treatment by allowing them enough latitude to tailor their treatments to each patient. The massage therapists will carefully document the treatments they actually provide using specially-designed treatment visit forms color-coded and customized for each type of massage. The therapists will provide treatments to participants in both the groups in their offices. Both massage treatment protocols will prescribe 10 visits over 10 weeks, with each follow-up visit lasting one hour. The first visit will be 75 to 90 minutes to allow for a full assessment as well as a treatment lasting 50 to 60 minutes.

In addition to providing the massage, therapists may prescribe self-care exercises from a pre-defined list of seven suggestions, which are designed to enhance the effects of the hands-on treatment. Six of these suggestions are common to both types of massage (see below). Massage therapists will demonstrate each self-care suggestion they make and ask the participant to practice the suggestion. In addition, participants will be provided a standardized handout describing and illustrating each suggestion.

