#### Stopping rules

The trial will be stopped only if the Data Safety Monitoring Body (DSMB) believes there is an unacceptable risk of serious adverse events in one or more of the treatment arms. In this case, the DSMB could decide to terminate one of the arms of the trial or the entire trial.

We are not proposing to perform an interim analysis for efficacy and therefore have established no formal stopping rules. Even if the two massage treatments reduce pain and dysfunction (the primary outcomes of this trial) more than usual care, we do not consider this an important enough reason to end the trial early. Previous trials of massage have been plagued by small sample sizes and we think it is important that this study be large enough and long enough to clearly evaluate the effectiveness of massage.

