#### Statistical Analysis

The primary statistical analyses will directly address Aim 1 (to determine if RM is an effective treatment for chronic low back pain) and Aim 2 (to determine if FSM is more effective than RM). A separate analysis will address the third aim, to explore the ability of psychosocial, and clinical baseline characteristics of patients to predict which of them will benefit most from each type of massage and which components of each treatment are associated with superior outcomes. These analyses are described below.

We will use an intent-to-treat approach for all analyses, i.e., individuals will be analyzed by the group to which they were randomized, regardless of participation in any treatment sessions. This minimizes biases that often occur when participants not receiving assigned treatments are excluded from analyses. We will use a standard linear regression mean model (ANCOVA) of the form:

where *Y*(*t*) is the response at follow-up time *t*, *Baseline *is the pre-randomization value of the outcome measure, *Trt *includes dummy variables for the full relaxation massage and focused structural massage groups, *Time *is a series of dummy variables indicating the follow-up times, and *z *is a vector of covariates representing other variables being adjusted for. (Note that α_1_, α_2_, α_3_, and α_4 _are vectors.) The referent group in this model is the usual care group at the first follow-up time. The models will be fitted using Generalized Estimating Equations (GEE) to take into account possible correlation within individuals over time [24]. GEE protects against misspecification of the correlation within a participant's scores over time. Such analyses can incorporate data for every time point at which a patient completes a follow-up interview. However, it is important to first assess whether there is differential dropout by either assigned treatment or symptom or function level. If differential dropout occurs, we will use the method of Little to rectify possible biases that could occur [25].

Both primary outcomes (function and symptoms) will be tested at the 0.05-level, because they address separate scientific questions. Analyses of both outcomes will be reported, imposing a more stringent requirement than simply reporting a sole significant outcome. Arguments against adjusting for multiple comparisons in this situation have been made by Rothman) and others [26-28].

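### Adverse experiences are asked about up to 11 times in the massage arms but once in usual care, over different reporting windows, so massage and usual-care counts are not comparable

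*Protocol article*

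**What the plan says.** The asking schedule is in the protocol article under Adverse Events: "Participants will be asked about adverse experiences at each massage visit and during the 10-week telephone interviews". Under Study Treatments, "Both massage treatment protocols will prescribe 10 visits over 10 weeks". Usual care has no study visits. Under Randomization to treatment groups, the contact described for that arm is by interview: "Participants randomized to the control group will be thanked for their willingness to participate, reminded of the importance of completing the follow-up interviews". In Table 3 (Assessment of outcomes), the row "Adverse experiences" is marked in the 10-week column only.

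The Adverse Events section also sets what will be left out of reporting: events that first appear "more than one week after a participant's final treatment (or more than 10 weeks after randomization for the usual care control group". The reason given is that the physiological effects of massage are fairly brief. The same section defines an adverse experience by its timing relative to massage and a plausible relation to it. It gives serious events an expedited route to the DSMB chair that covers the 10 weeks from randomization, and it promises that all adverse experiences will be summarized in routine DSMB and IRB reports.

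Under Stopping rules, the trial is stopped only if the DSMB "believes there is an unacceptable risk of serious adverse events in one or more of the treatment arms"; the board may then end one arm or the whole trial.

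**The concern.** A count of adverse experiences depends on how often people are asked, how far back they must remember, and how long events remain countable. All three differ between massage and usual care. Massage participants are asked roughly weekly while treated and again at 10 weeks; usual-care participants must recall 10 weeks in a single call. More frequent asking tends to raise the massage count.

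The window can pull the other way. In the massage arms it is tied to the participant's own last session, so it shortens for anyone who stops early, and some may stop because massage made them worse. A problem that first appears several weeks after stopping is not reported, although it falls within the period that is counted in usual care.

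Because usual care has a window of its own, its events are evidently meant to be counted, and readers of the safety summaries will set the arms side by side. They could not tell a real difference, or a real absence of one, from the effect of the collection scheme.

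**Working it through.** The article gives no figure for adverse-event ascertainment, so there is nothing of its own to reproduce. The check uses its schedule.

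**Asking occasions**
- Massage arms: 10 visits (Study Treatments) + 1 interview (Table 3) = at most 11.
- Usual care: 0 visits + 1 interview = 1.

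**Reporting window.** For the massage arms the article says "we will not report adverse events that first manifest more than one week after a participant's final treatment". I read the final treatment as the last massage received, and assume weekly visits counted from randomization. The window is then the week of the last massage + 1, against 10 weeks in usual care.

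| Last massage in week | Massage window (weeks) | Ratio to usual care |
|---|---|---|
| 1 | 2 | 0.2 |
| 2 | 3 | 0.3 |
| 3 | 4 | 0.4 |
| 5 | 6 | 0.6 |
| 8 | 9 | 0.9 |
| 10 | 11 | 1.1 |

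For a massage participant who never attends, there is no final treatment and the window is undefined. For someone who stops after visit 2, an event first appearing in week 5 falls outside the 3-week window; week 5 is inside the 10 weeks used for usual care.

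**Serious events.** Three statements in the Adverse Events section do not fit together for a participant who stops early. The expedited route runs for 10 weeks from randomization for any participant. The definition of a serious event confines it to events arising while treatment is under way. The general cut-off is one week past the last massage. A hospitalization in week 6 of someone last treated in week 2 meets the first condition but not the other two.

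**Illustration of unequal asking.** Expected recorded count = 133 × true risk × detection probability. Only the 133 per arm comes from the article; the true risk, taken as equal in all arms, and the detection probabilities are assumptions. The true risk cancels in the ratio of recorded rates, which equals the ratio of detection probabilities.
- Detection 0.90 (repeated asking) against 0.30 (one recall): ratio 0.90 / 0.30 = 3.0. At 10% true risk: 133 × 0.10 × 0.90 = 12.0 against 133 × 0.10 × 0.30 = 4.0 events.
- Detection 0.95 against 0.70: ratio 0.95 / 0.70 = 1.36. At 10% true risk: 133 × 0.10 × 0.95 = 12.6 against 133 × 0.10 × 0.70 = 9.3 events.

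This covers the asking effect only. The window effect depends on how many participants stop early, which the article does not give, so no net effect can be computed.

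**The case against.** The case against giving this much weight is substantial.

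- **No planned comparison is spoiled.** The article specifies no between-arm test or rate comparison of harms, and the outcomes listed under Statistical Analysis do not include them. This stands. A reader might infer that the scheme would probably produce a falsely significant harm difference. The documents do not support that: no such test is proposed, and the incidence and detection rates it would need have no source in the article.
- **The stopping rule rests on serious events.** Their expedited reporting period does not depend on attendance, and deaths or hospitalizations are less likely to be forgotten. This largely stands. A reader might infer that the DSMB's stopping decision is compromised; the documents do not go that far. What remains is that usual care has no scheduled inquiry before week 10, and the wording on serious events is not reconciled.
- **The definition is tied to massage.** Read strictly, a usual-care participant cannot have an adverse experience, so assuming equal true risk in all arms fits the definition poorly. This limits the illustration. It also shows another way in which the counts differ, since usual care is nevertheless given a window.
- **Intention to treat.** A reader might infer a contradiction with the rule that "individuals will be analyzed by the group to which they were randomized, regardless of participation in any treatment sessions". There is none. That rule governs the arm in which a person is analysed, and a cut-off on reported events moves nobody between arms. A window that depends on attendance is a weakness in its own right.
- **The asymmetry is partly inherent, and tabulation belongs in a fuller document.** Visits cannot be matched in an arm that has none, and for full completers the windows are close (about 11 against 10 weeks). But the asking schedule and both windows are fixed in the article itself, so this is not a detail left for elsewhere.

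**Conclusion.** The point holds for massage against usual care, as a worthwhile correction to safety reporting rather than a threat to the efficacy analysis. As written, the asking ratio is up to 11 to 1, and the massage window is about 0.2 to 1.1 times the usual-care window, given weekly visits counted from randomization. Counts from the two sides should not be compared, and following the rule drops later events in participants who stopped massage early. RM and FSM share one schedule and one rule and remain comparable with each other.

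The factor of 1.36 to 3.0 is illustrative only. It rests on assumed detection rates, ignores the opposing window effect, and should not be read as an expected bias.

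**What to change.** 1. State one fixed reporting window, counted from randomization, for all three arms whether or not massage was attended. This also settles the case of the participant who is never treated.
2. Base any massage-versus-usual-care display of adverse experiences on the 10-week interview alone, using the same neutrally worded items in every arm.
3. Report visit-elicited events separately, for RM versus FSM only, where asking is equal.
4. Reconcile the serious-event definition and the one-week cut-off with the 10-week expedited reporting period.

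The cost is some rewording of the Adverse Events section and a split of the safety table. No contacts are added, since the 10-week interview is already scheduled in every arm, and visit-level collection continues. The drawback is that the comparative table rests on less complete recall data and shows fewer events than a pooled count. Some asymmetry may also remain, because massage participants will have been prompted at earlier visits.
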